### Fidelity Data Analysis

The quantitative data from the fidelity index and questionnaire will be analyzed using descriptive statistics, including means and SD for continuous variables and absolute and relative frequencies for categorical variables.

### Qualitative Data Analysis

Interviews will be transcribed verbatim, translated into English, and analyzed using the Framework Approach [32], which is particularly useful for understanding and improving programs and policies and when multiple researchers are working with the data [33]. Excel (Microsoft Corp) software will aid in data handling.

Integration of interview findings with respective questionnaire data will be done using a “triangulation protocol” [34]. Methodological triangulation, where more than one research method or data collection technique is used [35], will be used in this study.

### Economic Evaluation

The feasibility of undertaking a full cost-effectiveness analysis will be assessed. This will primarily investigate the acceptability and resource use associated with capturing data for a cost-effectiveness evaluation in the full trial.

The team will capture costs associated with depression in NCD, such as delivery or receipt of the BIP. Costs will include the time to deliver the BIP and the cost of the materials used. And the costs of training the BA counselors to deliver the BIP will be calculated. Training requires the “staff time” of the trainer plus staff travel costs. Staff time is based on the salary of the trainer and allocated on a cost-per-minute basis, plus costs of materials.

Diaries to capture resource use, to be completed by patients and BA counselors, will be developed by the research team. Participants will be asked to complete these on a monthly basis for 3 months.

A pro forma to capture the costs of delivering the BIP incurred by the host organization will be completed by service managers, including staff salaries, time, and costs of estates and materials. An average cost per case per trial arm for treatment and the control group will be calculated.

Health service use will be assessed by asking pretested questions on contacts with doctors and nurses, hospital admissions, pharmacy visits, drug use, etc.

Quality of life will be assessed using a quality of life questionnaire (EQ-5D-5L) at baseline and 3 months. This information can be used as a quantitative measure of health outcomes as judged by the individual respondents. A higher score represents a better-perceived health state. The data will be checked for completeness.

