### Intervention Arm

Participants in the intervention arm will receive the BIP, delivered by trained nonmental health specialists (BA counselors) who will be specifically recruited for the study. BA counselors will be supervised by a mental health specialist.

The BIP will be delivered over 6 sessions lasting 30-40 minutes over a period of 6-12 weeks, with a minimum of one week between sessions. All sessions will be delivered remotely, by telephone. An alternate telephone number will be collected at the time of recruitment to ensure the unhindered delivery of BA sessions to the client.

The components of BIP include structured sessions where participants, with the BA counselors, plan and identify 3 types of activities. The first one includes routine and necessary activities that are done either regularly or on a daily basis, for example, getting fresh, taking a bath, cooking, doing household chores, etc. Second, social activities involve interacting with other people, for example, meeting or chatting with people from the neighborhood, etc. And third, pleasurable activities include activities that one enjoys and has fun with. For example, reading a newspaper or book, watching television (serials and movies), etc. The BA counselor and the participant will both have a flipbook for guidance and a better understanding of the activities during the session, as it contains a pictorial representation of each type of activity. The BA counselor will follow a manual and maintain the session logs of the participants. The BA counselor in the session log will not only maintain the session details but also keep a record of the daily activities done by the participants and the mood associated with doing these activities through telephonic follow-up in between the sessions. Another reason this is done is to check if the participants are doing the activities or if they are facing any challenges while doing them.

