### Ethical Considerations

Ethics and other relevant approvals on the protocol have been secured from the University of York Health Sciences Research Governance Committee (HSRGC/2020/418/B; November 27, 2020); the Health Ministry Screening Committee, India (2020-9330; June 12, 2020); and the ethics committee, NIMHANS’s Behavioral Sciences Division (NIMHANS/EC [BEH. SC.DIV.] 22nd MEETING/2OI9; February 3, 2020). The trial is also registered under the Clinical Trial Registry of India (CTRI/2020/05/025048; May 6, 2020).

Approvals for necessary amendments adjusting to the COVID-19 pandemic situation have been provided by the institutional ethics committee, Behavioral Sciences Division, NIMHANS.

The following amendments are made to the protocol:

In the first amendment to the protocol dated September 25, 2020, the focus group discussions and interviews as part of the survey of organizational capacity were shifted from face-to-face to telephonic mode.In the second amendment to the protocol dated May 15, 2021, the recruitment process was shifted from face-to-face to telephonic mode, and NCD counselors were involved in preliminary screening. A total of 4 BA counselors of the same cadre as the NCD counselors were recruited into the study to deliver the BA sessions.In the third amendment to the protocol dated January 27, 2022, process evaluation interviews are to be conducted at 8 weeks instead of 12 weeks, that is, immediately after the participants in the intervention group complete their 6 BA sessions and in the control group at 8 weeks after the participants receive their brief advice from the RAs postbaseline assessment.

Participants in the intervention group will receive INR 250 (US $3.01) per session, and participants in the EUC group will receive INR 250 (US $3.01) for attending the one-time brief advice.

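### The training-cost rule has no term for the time of the four BA counselors being trained, so the training cost is understated by an amount the protocol does not let one compute

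*Protocol article*

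**What the plan says.** In its Economic Evaluation section the protocol article commits to a training cost: "And the costs of training the BA counselors to deliver the BIP will be calculated". It then says what goes into it: "Training requires the “staff time” of the trainer plus staff travel costs. Staff time is based on the salary of the trainer". In full, the valuation is: "Staff time is based on the salary of the trainer and allocated on a cost-per-minute basis, plus costs of materials".

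The people being trained are described elsewhere. Under Intervention Arm, the BIP is "delivered by trained nonmental health specialists (BA counselors) who will be specifically recruited for the study". Under Ethical Considerations, the second protocol amendment gives their number: "A total of 4 BA counselors of the same cadre as the NCD counselors were recruited into the study to deliver the BA sessions".

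The Economic Evaluation section has three other sources that could bear on counselor time:
- a BIP cost item for delivery time and materials;
- resource-use diaries for patients and BA counselors, still to be developed;
- a pro forma, completed by service managers, for what delivery costs the host organization, including salaries and time.

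None of the three mentions time spent in training.

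**The concern.** The quantity named is the cost of training the counselors. The rule attached to it prices the provision of a trainer, with travel and materials. Training uses the time of two groups, those who teach and those who are taught, and only the first has a term.

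The intervention rests on task shifting to counselors who are not mental health specialists, so training them is a core set-up input. Leaving out their time biases the training cost in one direction, downward. For group training, the uncounted share of time grows with the number of counselors per trainer. The economic component exists to prepare data capture for a cost-effectiveness evaluation in the full trial, so an input missing from the rule here could stay missing there.

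**Working it through.** The article states no training cost, hours, salaries or number of trainers, so there is no figure of the plan's own to reproduce. The check has two parts.

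**1. Is trainee time captured anywhere in the Economic Evaluation section?**

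| Source | What it covers | Trainee time stated? |
|---|---|---|
| Training-cost rule | Trainer time at trainer salary per minute, staff travel, materials | No |
| BIP cost item | Time spent delivering the intervention, and materials | No; training is costed as a separate item |
| Counselor diary | Resource use; content still to be developed | Neither included nor excluded |
| Service managers' pro forma | Host organization's costs of delivery, including salaries and time | Not stated; the counselors were recruited for the study |

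No source is stated to supply the missing term.

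**2. How large could the omission be?**

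Input from the article: 4 counselors (Ethical Considerations, second amendment).

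Assumptions, none given in the article:
- each counselor attends the whole course, whose length is set to 1 unit;
- k = number of trainers;
- c = contact units per trainer (1 for group teaching, 4 for one-to-one);
- p = preparation time per trainer, in course lengths.

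Share of person-time omitted = 4 / (4 + k(c + p)).

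| Format | k | p | Calculation | Share omitted |
|---|---|---|---|---|
| Group | 1 | 0 | 4/5 | 80% |
| Group | 2 | 0 | 4/6 | 67% |
| Group | 3 | 0 | 4/7 | 57% |
| Group | 4 | 0 | 4/8 | 50% |
| Group | 1 | 1 | 4/6 | 67% |
| Group | 1 | 2 | 4/7 | 57% |
| Group | 2 | 1 | 4/8 | 50% |
| One-to-one | 1 | 0 | 4/8 | 50% |
| One-to-one | 1 | 1 | 4/9 | 44% |

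A share of person-time is not a share of cost. Let r be the trainer's pay per minute divided by the counselor's, also an assumption. For group teaching without preparation time, the omitted share of staff-time cost = 4 / (4 + k·r):
- k = 1: r = 1 gives 4/5 = 80%; r = 2 gives 4/6 = 67%; r = 3 gives 4/7 = 57%; r = 5 gives 4/9 = 44%.
- k = 2: r = 1 gives 4/6 = 67%; r = 2 gives 4/8 = 50%; r = 5 gives 4/14 = 29%.

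Travel and materials are left out of these shares. Both are in the rule, so the omitted share of the full training cost would be lower.

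**The case against.** A journal article condenses a fuller protocol, and a two-sentence account of costing inputs need not be exhaustive. It contains no word such as only and no formula. This has some weight, but it does not settle the matter: the article goes beyond saying that training will be costed. It lists components and ties staff time to the trainer's salary, and that list does not match the quantity it is meant to price.

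The diary or the pro forma might also pick up training hours. The monthly, three-month diary schedule is stated for participants and not clearly for counselors, so it cannot be used to rule the counselor diary out. The Data Management section also describes the purpose of the economic data more broadly, as evidence on what it costs to provide the BIP in the host institution. Capture is therefore possible, but nowhere stated.

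A reader might infer more than the article supports:
- That most of the person-time is missed. This depends on trainer numbers, format and preparation time. The share is 50% or less with one-to-one teaching, with four or more trainers, or with two trainers whose preparation equals contact time.
- That the omitted time is paid. The article says the counselors were recruited for the study and is silent on pay during training. If that time was unpaid, the case rests on its opportunity cost.
- That the rule counts nothing but the trainer. This is true of the time component alone. Travel and materials are included, and the travel term is not limited to the trainer.
- That a conclusion of the trial is at risk. The economic component mainly tests data capture, and no progression criterion or cost-effectiveness result is said to depend on the training cost.

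**Conclusion.** The point holds in limited form. The written rule omits the time of the four BA counselors in training, and no other cost source in the section is stated to capture it. A training cost calculated by this rule is too low. The direction needs only that the counselors' time has some value and is not added from another source. The amount cannot be computed from the article; the 80% and 50% figures for one trainer illustrate the scale under stated assumptions and are not estimates.

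The consequence is confined to the costing output that feeds the full trial's economic evaluation. Recruitment, retention, fidelity and PHQ-9 results are untouched. The correction is worth making because it is specific and cheap, and because preparing that evaluation is what the economic component is for.

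**What to change.** Either of two changes would do:

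1. Add a term to the training-cost rule in the Economic Evaluation section: counselor time in training = hours attended × 60 × counselor salary per minute, summed over the counselors, alongside trainer time, staff travel and materials. Report the training cost in total and per counselor trained.
2. If the counselor diary or the service managers' pro forma is meant to capture this time, say which one does and include the amount in the reported total, counted once.

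The cost is about a sentence of text and a small calculation, with no new data from participants. BIP development ended on August 18, 2021, and quantitative data collection on December 10, 2021, so training hours may have to be reconstructed from study records; the article does not say which records exist. Analyses were still under way at publication, so the change remained possible then. The downside is a higher, less favourable training cost.

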### Data Management

The following data will be collected from feasibility trial participants (at baseline and 3-month follow-up): demographic data and validated instrument measurements of mental and physical health. The process evaluation of the feasibility trial will collect data from interviews with trial participants and BA counselors, a sample of audio-recorded BIP sessions, and drop-out data. Health economic data will be collected to provide evidence of the costs of providing the BIP in the host institution.

All study data will be stored in accordance with the General Data Protection Regulation and the University of York data management policies. Electronic data will be password-protected and stored on secure servers at the country’s partner institutions and the University of York.

Unique study identification (ID) numbers, allocated by the research team, will be used to anonymize data on electronic documents containing data from the trial and interviews. Paper-based documents, for example, consent forms and hard copies of transcripts, as well as any research participant personal data collected, will be stored in locked filing cabinets at the partner institutions.

Study documents (paper and electronic) at the research sites will be retained in a secure (locked when not in use) location during and after the study finishes. Interview recordings will be transferred from the digital recorder to a secure server as soon as possible after the interview has taken place. Once the transferred recording has been checked to ensure audibility, the original will be deleted from the digital recorder. All essential documents, including source documents (eg, transcripts), will be retained for a minimum period of 10 years after study completion, in accordance with the University of York Research Data Management Policy. This is deemed to be sufficient time for any queries arising from the findings to be answered, for example, queries arising from the publication of the findings. They will be retained in secure locations (locked when not in use) at the University of York and at the partner institutions.

The Department of Health Sciences at the University of York has a backup procedure approved by auditors for disaster recovery. There will be a separate archive of electronic data performed at the end of the study to safeguard the data and comply with regulatory requirements. The access, use, and storage of sensitive or confidential data will be conducted in accordance with the University of York Data Security Policy and Handling Sensitive Data Guidance. All sensitive or confidential data used for BEACON will be encrypted.

### Data Monitoring

Data will be monitored for quality and completeness by the delegated researchers at the study site, followed by a second check by researchers at the University of York using verification, validation and checking processes. Missing data will be pursued until the study’s end unless it causes any distress to the participant contacted. Data will be reported to the Health Ministry Screening Committee and Ethics Committee as required.

### Adverse Events

Working with a potentially vulnerable group of participants has many ethical implications. We have addressed them in our ethics application. The main adverse events anticipated in this study, both during the recruitment phase and during the delivery of the BIP, are self-harm and suicide risk. Therefore, standard operating procedures to address these adverse events will be adapted by the study team.

#### Informed Consent

As the recruitment is done at 2 levels, written consent will be obtained at first-level screening using PHQ-2 [22] by the staff (NCD counselors and nurses) and verbal consent for the next level screening using PHQ-9 [23] by the RAs.

#### Privacy and Confidentiality

Data will be anonymized, replacing identifiable personal data with unique study participant identification numbers, with the key only available to the local research team and the principal investigator.

### Community Engagement

A community advisory panel will provide community engagement and involvement for the duration of the study. This panel consists of patient and family representatives and community and voluntary sector advocates interested in improving the care of common mental disorders and NCDs. The panel has already given feedback on:

The accessibility and feasibility for patients of the proposed BIP intervention, including remote delivery.Delivery of BA counseling by the NCD counselors.The acceptability of proposed methods for the feasibility trial.

The feedback and suggestions were incorporated into the intervention development and delivery plans of the study. The panel will continue to provide feedback, providing an important perspective on the delivery of the study and its findings.

### Dissemination

Feasibility study results will be disseminated by engaging end users of our research, including policy makers and commissioners, by holding knowledge transfer and dissemination events at key stages. Lay summaries and fact sheets of findings are distributed using social media, newspapers, and a project website, alongside publications in academic journals, to reach a range of audiences.

### Ethical Considerations

Ethics and other relevant approvals on the protocol have been secured from the University of York Health Sciences Research Governance Committee (HSRGC/2020/418/B; November 27, 2020); the Health Ministry Screening Committee, India (2020-9330; June 12, 2020); and the ethics committee, NIMHANS’s Behavioral Sciences Division (NIMHANS/EC [BEH. SC.DIV.] 22nd MEETING/2OI9; February 3, 2020). The trial is also registered under the Clinical Trial Registry of India (CTRI/2020/05/025048; May 6, 2020).

Approvals for necessary amendments adjusting to the COVID-19 pandemic situation have been provided by the institutional ethics committee, Behavioral Sciences Division, NIMHANS.

The following amendments are made to the protocol:

In the first amendment to the protocol dated September 25, 2020, the focus group discussions and interviews as part of the survey of organizational capacity were shifted from face-to-face to telephonic mode.In the second amendment to the protocol dated May 15, 2021, the recruitment process was shifted from face-to-face to telephonic mode, and NCD counselors were involved in preliminary screening. A total of 4 BA counselors of the same cadre as the NCD counselors were recruited into the study to deliver the BA sessions.In the third amendment to the protocol dated January 27, 2022, process evaluation interviews are to be conducted at 8 weeks instead of 12 weeks, that is, immediately after the participants in the intervention group complete their 6 BA sessions and in the control group at 8 weeks after the participants receive their brief advice from the RAs postbaseline assessment.

Participants in the intervention group will receive INR 250 (US $3.01) per session, and participants in the EUC group will receive INR 250 (US $3.01) for attending the one-time brief advice.

## Results

The BIP was developed beginning on November 28, 2020, and it was finished on August 18, 2021. The quantitative data-gathering process began on August 23, 2021, and was finished on December 10, 2021, following the acquisition of approval from all pertinent agencies. Process evaluation (qualitative data) collection is ongoing. Both the qualitative and quantitative data analyses are ongoing.

## Discussion

### Overview

This research study overall aims to address the evidence gap regarding the use of BA for depression in people with NCDs by adapting BA interventions to the Indian context, testing the acceptability, feasibility, and implementation of adapted BA intervention, and testing the feasibility of a randomized controlled trial evaluation of BIP for the treatment of depression compared with EUC.

Effective treatment of depression in NCDs offers the potential to improve mental and physical outcomes for this population and, additionally, maximize the efficient use of health care resources. To bridge the treatment gap globally, psychological therapies must be scaled up, which necessitates their effective use in many cultural contexts. An increasing number of studies have examined the degree to which cultural adaptation enhances the acceptability and effectiveness of psychological therapies among populations from various cultural backgrounds. The data are still unclear at this stage because there are not enough studies that analyze the many types of changes involved in cultural adaptation [36]. If shown to be effective, the approach of integrating treatment for a mental disorder within NCD care will also provide the opportunity to harness physical health resources to reduce the large mental health treatment gap, reduce stigma for people with mental illness, and add to the data on cultural adaptation of interventions such as BA.

Several of the issues with conventional psychological therapy may be resolved through remote therapy. Because of their accessibility and simplicity, telephone-based therapies are a popular research topic in the field of therapeutic communication and may provide important advantages. Data suggests that a therapeutic connection and successful treatment outcomes may not require the colocation of a patient and therapist. Nonetheless, the evidence is scant in both amount and quality [37]. Therefore, this study might provide evidence of how well BA can be delivered remotely and whether this approach can be further scaled up.

If the feasibility trial demonstrates that the BIP is feasible and potentially beneficial, we will be able to make further adaptations to the BIP and test the intervention in a full trial.

